## Abstract

**Background:**

Diabetic peripheral neuropathy (DPN) is the most common chronic complication of diabetes mellitus that has a considerable impact on quality of life, but there are few effective therapeutic strategies. The aim of this trial is to determine the efficacy and safety of manual acupuncture (MA) versus sham acupuncture (SA) for DPN.

**Methods/design:**

This is a study protocol for a randomized, placebo-controlled clinical trial. A total of 118 patients with DPN will be recruited and randomly assigned in a 1:1 ratio to either the MA group or SA group. All patients will receive 24 sessions over 12 weeks. Participants will complete the trial by visiting the research center at month 6 for a follow-up assessment. The primary outcome is peroneal motor nerve conduction velocity (peroneal MNCV) at week 12 compared with baseline. Secondary outcomes include peroneal motor nerve action potential amplitude (peroneal MNAP) and latent period (peroneal MNLP), sural sensory nerve conduction velocity (sural SNCV), action potential amplitude (sural SNAP) and latent period (sural SNLP), fasting plasma glucose (FPG), 2-h postprandial blood glucose (2hPG), glycated hemoglobin (HbAlc) at week 12 compared with baseline, Michigan Neuropathy Screening Instrument (MNSI) score and Diabetes Specific Quality of Life scale (DSQL) at week 12 and month 6 compared with baseline. Safety will be assessed during the whole trial. Masking effectiveness will be assessed by patients.

**Discussion:**

This trial may provide high-quality evidence for evaluating the efficacy and safety of MA treatment for DPN compared with SA treatment. Results of this study will be published in peer-reviewed journals.

**Trial registration:**

Chinese Clinical Trials Registry ChiCTR1800020444. First registered on 29 December 2018, retrospectively registered, http://www.chictr.org.cn/showproj.aspx?Proj=31063.

## Background

Diabetic peripheral neuropathy (DPN) is the most common cause of neuropathy worldwide, and its prevalence increases with the duration of diabetes [1]. Approximately 50% of patients with diabetes will develop peripheral neuropathy [1–3]. DPN is symmetric and predominantly sensory, starting distally and gradually spreading proximally in a glove-and-stocking distribution [1]. DPN is associated with the development of foot problems such as foot ulcers and is one of the leading causes of amputations. The high-frequency underreport and undertreatment of DPN can lead to an increased risk for morbidity and mortality and decreased quality of life [1, 2]. Once symptoms appear, there are few effective therapeutic strategies [4]. While neuropathic pain and paresthesia can be palliated by anti-convulsant drugs, tricyclic antidepressant drugs, or serotonin-noradrenalin re-uptake inhibitors [5], pharmacological management of decreased sensation is generally ineffective. Therefore, more and more patients turn to seek non-pharmacological treatments. Multiple complementary and alternative medicine therapies such as acupuncture and yoga have shown efficacy in the treatment of painful peripheral neuropathy [6]. A pilot RCT has demonstrated practicality and feasibility of acupuncture as an additional well-tolerated treatment without appreciable side effects for people with DPN [7]. Acupuncture may effectively ameliorate selected DPN symptoms, such as aching pain, burning pain, prickling sensation, numbness, and allodynia in American Indian patients [8]. Reviews concerning acupuncture for peripheral neuropathy (PN) have found that, despite the majority of studies reporting positive results, a reliable statement of effectiveness is not possible due to methodological limitations such as unsuitable control group and blinding [9–11]. Also, inconsistency of outcome measures and lack of use of global neuropathy-specific patient-reported outcome measures have confounded results. Overall, the quality of acupuncture intervention delivered in individual studies was low. Appropriately powered RCTs with suitable control groups, validated and proper outcome measures for DPN patients, and more accurate reporting of acupuncture interventions, including point selection rationales, point locations, and practitioner qualifications, are needed. Therefore, we have designed a randomized, sham-controlled, participant-blinded and assessor-blinded study with a 6-month observation period to explore its effectiveness and safety.

## Methods

### Study design

This randomized, participant-blind, sham-controlled trial will be conducted at Long-Hua Hospital affiliated to Shanghai University of Traditional Chinese Medicine in China. The protocol for this trial is reported based on the Standard Protocol Items: Recommendations for Interventional Trials (SPIRIT) 2013 Checklist: defining standard protocol items for clinical trials (Additional file 1). The study has been approved by the Ethics Committee of Long-Hua Hospital (Ethical approval number: 2016LCSY028) and registered on the Chinese Clinical Trial Registry (Chictr) platform since 29 December 2018 (Registration number: ChiCTR1800020444). A flow diagram of the trial is shown in Fig. 1.

**Fig. 1 Fig1:**
[figure not shown]
Flow diagram

### Patient recruitment

Patients meet the American Diabetes Association (ADA) 2012 diagnostic criteria for DPN will be recruited from the endocrinology departments of Long-Hua Hospital affiliated to Shanghai University of Traditional Chinese Medicine in Shanghai, China. Recruitment posters will be posted in the hospital and uploaded to social media (WeChat) from October 2016 to December 2021. All patients will be required to provide written informed consent (Additional file 2) before randomization.

### Inclusion criteria

Participants who meet all the following requirements will be allowed for enrollment:
Aged 18–75 years (either sex)Patients who meet diagnosis of DPN defined by ADA in 2005 [12]
DPN is defined as the presence of symptoms and/or signs of peripheral nerve dysfunction in people with diabetes, after the exclusion of other causesNP is defined as altered sensitivity to pressure and (1) altered sensitivity to pain or (2) altered sensitivity to vibration or (3) achilles reflex [13]Symmetric and predominantly sensory, starting from the lower limbs distally and gradually spreading proximally in a glove-and-stocking distributionAbility to understand study procedures and willingness to comply with them for the entire period of studyWritten informed consent

### Exclusion criteria

Participants meeting any of the following criteria will be excluded:
PN caused by conditions other than diabetes (e.g., alcohol abuse, chemotherapy, hereditary causes, chronic inflammatory, or idiopathic PN)Psychiatric illnesses other than mild depressionSevere or unstable cardiovascular, liver, kidney, respiratory, or hematological disordersReceived acupuncture treatment in the last 3 monthsPregnant or lactating womenResearch unit personnel directly related to the study and their immediate family membersIncapable of giving informed consent or following the study instructions due to language disturbances, serious cognitive deficits, or lack of timeCurrently participating in other clinical trials

### Randomization and allocation concealment

All eligible patients will be randomly assigned to manual acupuncture (MA) group or sham acupuncture (SA) group in a 1:1 ratio. The blocked randomization sequence will be computer-generated (Excel) by an independent statistician, who will not be involved in implementation and statistical analysis of the trial. The allocation will be placed inside sequentially numbered sealed opaque envelopes which will be opened only after enrollment. The treatment allocation will be revealed to acupuncturists out of patients’ sight to ensure blinding. To reduce the risk of observer bias, the acupuncture practitioners will be discouraged from discussing treatments or previous results with patients. The random allocation sequence and sealed opaque envelopes will be kept separately by two specific researchers. The clinical research coordinator will be responsible for enrolling patients, obtaining informed consent, and requesting randomization.

### Masking

Due to the nature of acupuncture, masking of acupuncturists is quite difficult to achieve. Patients, outcome assessors, and statisticians who perform the statistical analyses will be blinded to group assignment. The treatments subjects received will be not revealed until the statistical analysis is completed.

### Interventions

Treatment will be performed by licensed acupuncturists who have at least 5 years of experience in acupuncture. All the acupuncturists will be trained how to locate acupoints, puncture, and manipulate needles before trials. A placebo device [14, 15] will be applied in both groups for better implementation of blindness. Both MA and SA treatments will consist of 24 sessions over 12 weeks (40 min per session, two sessions per week). Acupuncture will be discontinued if patients suffer from any serious adverse events (AEs).

### Manual acupuncture

Patients allocated to the MA group will receive treatment with needles being inserted at the prespecified acupuncture points through the placebo device. Obligatory and additional acupoints adopted in this protocol are developed from clinical experiences of acupuncture experts. The obligatory acupoints include Zhongwan (CV12), bilateral Weiwanxiashu (EX-B3), bilateral Ganshu (BL18), bilateral Pishu (BL20), bilateral Shenshu (BL23), bilateral Zusanli (ST36), bilateral Yanglingquan (GB34), bilateral Sanyinjiao (SP6), bilateral Taixi (KI3), and Bafeng (EX-LE10). Additional acupoints Baxie (EX-UE9) will be added when patients’ symptoms appear not only in the lower limbs but also in the upper limbs. All acupoints are localized according to the WHO Standard Acupuncture Locations and exhibited in Table 1 and Fig. 2. After skin disinfection, disposable, stainless steel acupuncture needles (0.25 × 25 mm or 0.25 × 40 mm, provided by Wuxi Jiajian Medical Instrument Co. Ltd., China) will be inserted into the skin of acupoint (approximately 10–20 mm depth), and then manipulations of twirling, lifting, and thrusting will be performed on all needles for at least 10 s to reach De qi (a compositional sensation including soreness, numbness, distention, and heaviness), which is believed to be an essential component for acupuncture efficacy. Firstly, CV12, ST36, GB34, SP6, KI3, EX-LE10, and EX-UE9 will be punctured when patients lie supine. Then, EX-B3, BL18, BL20, and BL23 will be punctured when patients lie prone. Needles will be retained in these acupoints for 20 min.

**Table 1 Tab1:** Locations and manipulations of acupoints

	Acupoint	Location	Manipulation
Obligatory acupoints	Zhongwan (*CV12*)	On the anterior midline, 4 cun^a^ above the umbilicus	Puncture perpendicularly to a depth of 1.0–1.2 cun
	Weiwanxiashu (*EX-B3*)	at the same level as the inferior border of the spinous process of the 8th thoracic vertebra (T8), 1.5 cun lateral to the posterior median line	Puncture obliquely and medially to a depth of 0.5–0.8 cun
	Ganshu (*BL18*)	at the same level as the inferior border of the spinous process of the 9th thoracic vertebra (T9), 1.5 cun lateral to the posterior median line	Puncture obliquely and medially to a depth of 0.5–0.8 cun
	Pishu (*BL20*)	at the same level as the inferior border of the spinous process of the 11th thoracic vertebra (T11), 1.5 cun lateral to the posterior median line	Puncture obliquely and medially to a depth of 0.5–0.8 cun
	Shenshu (*BL23*)	at the same level as the inferior border of the spinous process of the 2nd lumbar vertebra (L2), 1.5 cun lateral to the posterior median line	Puncture perpendicularly to a depth of 0.8–1.2 cun
	Zusanli (*ST36*)	3 cun directly below Dubi (*ST35*), and one finger-breadth lateral to the anterior border of the tibia	Puncture perpendicularly to a depth of 1.0–1.2 cun
	Yanglingquan (*GB34*)	in the depression anterior and distal to the head of the fibula	Puncture perpendicularly to a depth of 1.0–1.2 cun
	Sanyinjiao (*SP6*)	3 cun superior to the prominence of the medial malleolus, posterior to the medial border of the tibia,	Puncture perpendicularly to a depth of 1.0–1.2 cun
	Taixi (*KI3*)	in the depression between the prominence of the medial malleolus and the calcaneal tendon	Puncture perpendicularly to a depth of 0.5–0.8 cun
	Bafeng (*EX-LE10*)	on the dorsum of the foot, between the first and fifth toes at the junction of the red and white skin posterior to the margin of the web; 4 points on each foot, 8 in total	Puncture obliquely to a depth of 0.5–0.8 cun
Additional acupoints for upper limbs syndrome	Baxie (*EX-UE9*)	at the dorsum of the hand, between the first and fifth fingers, proximal to the web margins between the five fingers at the junction of the red and white skin, 4 points on each hand,8 in total	Puncture obliquely upward to a depth of 0.5–0.8 cun

^a^1 cun (≈ 20 mm) is defined as the width of the interphalangeal joint of patient’s thumb

**Fig. 2 Fig2:**
[figure not shown]
Locations of acupoints

### Sham acupuncture

Patients in the SA group will receive sham acupuncture. The procedure and duration of treatment in the SA group will be identical in the MA group except the needles (0.25 × 25 mm, blunt tip, provided by Wuxi Jiajian Medical Instrument Co. Ltd., China) are blunt tip and there will be no skin penetration and needle manipulation for De qi.

Although it is difficult to set an eligible placebo control, using blunt-tipped needles that do not penetrate the patient’s skin is the most common approach for administering sham treatments among acupuncture trials, according to a literature review [16, 17]. Moreover, this study will exclude those who have received acupuncture treatment in the last 3 months and can distinguish SA from MA. The same control with no skin penetration at acupoints was adopted and succeeded in masking patients with DPN [7, 14, 15, 18]. Furthermore, all patients will be asked to guess which treatment they have received to test the patient-blinding effects at week 12.

### Concurrent treatments

Participants will receive routine health care as provided to all other patients with DPN. These treatments include glucose control, antihypertensive therapies, dyslipidemia control, analgesic, and neurotrophic treatments, if necessary. All information regarding the use of medications (including date of administration, types, and dosage) will be recorded. This will contribute to improving adherence.

### Follow-up

After 12-week treatments, all participants will enter an additional 3 months follow-up period. During this time, they will receive routine health care as provided to all other patients with DPN. However, acupuncture treatment will not be permitted during follow-up.

### Outcomes

#### Primary outcome

The primary outcome is peroneal motor nerve conduction velocity (peroneal MNCV) which will be assessed at baseline and at week 12 after randomization.

#### Key secondary outcomes

Secondary outcomes include peroneal motor nerve action potential amplitude (peroneal MNAP) and latent period (peroneal MNLP), sural sensory nerve conduction velocity (sural SNCV), action potential amplitude (sural SNAP), and latent period (sural SNLP). The outcome measurements will be assessed at baseline and at week 12 after randomization.

Additional secondary outcomes include glycated hemoglobin (HbA1c), fasting plasma glucose (FPG), 2-h postprandial blood glucose (2hPG), body mass index (BMI), and blood pressure (BP). The outcome measurements will be assessed at baseline and at week 12 after randomization.

### Michigan Neuropathy Screening Instrument (MNSI) score

The MNSI is a clinical and semi-quantitative evaluation of neuropathy that includes medical history and physical assessment. Medical history will be completed by patients with scores ranging between 0 and 13. Physical assessment will be completed by health professionals with five indicators and the aggregate score ranging between 0 and 10: foot appearance (0 and 1 for normal and abnormal, respectively), ulceration (0 and 1 for normal and abnormal, respectively), ankle reflex (0, 0.5, and 1 for normal, reenforced, and absent, respectively), vibration test (0, 0.5, and 1 for normal, weakened, and absent, respectively), and monofilament examination (0, 0.5, and 1 for normal, weakened, and absent, respectively) of feet on both sides. The outcome measurement will be assessed at baseline, at week 12 and at month 6 after randomization.

### Quality of life (QoL)

Disease-specific QoL will be assessed at baseline and at week 12, month 6 after randomization using Diabetes Specific Quality of Life scale (DSQL). The scale consists of four domains: interference (12 items), psychology (8 items), social relations (4 items), and treatment (3 items). Each item is measured with a 5-point Likert scale ranging from “not at all” to “extremely”. Higher scores indicate worse QoL.

### Patients’ global assessment of DPN

Patients’ global assessment of DPN will be evaluated on a 5-point Likert scale at week 12. Patients will be asked to respond to the following question: “Considering all the ways your DPN affects you, how are you doing today?” 1 = very poor; 2 = poor; 3 = fair; 4 = good; or 5 = very good.

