#### Statistical analysis

Statistical analysis will be performed by an independent statistician who is not aware of group allocation. SPSS 21.0 (IBM SPSS Statistics, New York, USA) will be used for data analysis. Level of significance will be established at α < 0.05 with a two-sided test. Continuous data will be represented by mean ± standard deviation or median (range), and categorical data will be represented by percentage. All efficacy analyses will be performed using the intent-to-treat (ITT) approach. For the ITT analysis, population will consist of all patients who have been randomized. Missing data will be imputed using the last observation carried forward (LOCF) method. Continuous variables will be compared using Student’s *t* test or Wilcoxon rank-sum test as appropriate. Categorical variables will be compared using Fisher’s exact test or Wilcoxon rank-sum test as appropriate. Analysis of covariance (ANCOVA) or logistic regression will be used for analysis and adjustment of baseline characteristics that differ significantly between two groups.

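### The patients' global assessment is a current-status item taken only at week 12, and it is the only efficacy outcome with no stated baseline

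*Protocol article*

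**What the plan says.** The section on the patients' global assessment fixes both timing and wording. On timing: "Patients’ global assessment of DPN will be evaluated on a 5-point Likert scale at week 12". On wording, the patient answers "Considering all the ways your DPN affects you, how are you doing today" on five grades, from 1 (very poor) to 5 (very good). No baseline or month-6 reading is mentioned.

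The other efficacy outcomes are scheduled differently:

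- Primary outcome, peroneal MNCV: "which will be assessed at baseline and at week 12 after randomization".
- The remaining nerve conduction measures, glycaemic measures, BMI and blood pressure: "The outcome measurements will be assessed at baseline and at week 12 after randomization".
- MNSI: "The outcome measurement will be assessed at baseline, at week 12 and at month 6 after randomization".
- DSQL: "Disease-specific QoL will be assessed at baseline and at week 12, month 6 after randomization".

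The abstract's list of secondary outcomes, which are framed as comparisons with baseline, does not include the global assessment. The article promises no change score for it.

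**The concern.** An item worded as change since the start of treatment can do without a baseline, because the patient supplies the comparison. This item asks about the present state. A patient who answers 3 at week 12 may have come up from 1 or down from 5, and the data cannot tell which.

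Three things are lost. The item cannot be reported as change within patients. A chance difference between the arms on this item at entry cannot be seen directly or adjusted for directly. And the arm comparison carries variation between patients that a baseline reading would have explained. The entry criteria are broad (ages 18 to 75, symptoms and/or signs of neuropathy), so some spread at entry is to be expected.

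This is a matter of which data are collected. An analysis plan written later cannot recover an answer that was never asked for.

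**Working it through.** **The plan's own figure.** The Sample size section gives a difference of 2.4 m/s, an SD of 4.15 m/s, alpha 0.05 (two-sided according to the Statistical analysis section) and 80% power. With the normal approximation:

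n per arm = 2 × (1.960 + 0.842)² × 4.15² / 2.4² = 2 × 7.849 × 17.22 / 5.76 = 46.9, so 47.

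Allowing for drop-out, 47 / 0.80 = 58.75, so 59 per arm and 118 in total. The stated figures reproduce (the t-distribution version gives 47.9, so 48). They concern the primary outcome and are used here only as the number of evaluable patients per arm.

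**Schedule check.** Of the efficacy outcomes, peroneal MNCV, the other conduction measures, the glycaemic measures, BMI, blood pressure, MNSI and DSQL all have a baseline. The global assessment alone has none. The other items without a before-and-after pair (blinding guess, credibility and expectancy, safety rating, needling sensation, medication log) are not efficacy outcomes.

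**Precision.** Let r be the correlation between the same item at baseline and at week 12. The article does not give r; 0.3 to 0.6 is assumed. Treating the five grades as a score, adjustment for baseline leaves a fraction 1 − r² of the week-12 variance, and 47 adjusted patients per arm are worth 47 / (1 − r²) unadjusted ones. The difference detectable with 80% power is 2.802 × √(2/47 × (1 − r²)) in units of the week-12 SD.

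| r | Variance removed, r² | Unadjusted equivalent of 47 per arm | Detectable difference (SD) |
|---|---|---|---|
| 0 (no baseline) | 0% | 47 | 0.58 |
| 0.3 | 9% | 47 / 0.91 = 51.6, about 52 | 0.55 |
| 0.6 | 36% | 47 / 0.64 = 73.4, about 73 | 0.46 |

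**Missing data (a side note, not part of the size above).** The Statistical analysis section says "Missing data will be imputed using the last observation carried forward (LOCF) method" and, on the population, "For the ITT analysis, population will consist of all patients who have been randomized". An outcome measured once has no earlier value to carry forward. At the planned drop-out, up to 118 − 2 × 47 = 24 patients could lack a week-12 answer, and the stated rule would give them none.

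**The case against.** The strongest reply is that nothing here is invalid. Allocation is randomised 1:1 and concealed, so comparing week-12 status between arms estimates the treatment effect without bias. The protocol promises no change analysis for this item and claims no power for it. A status comparison at the end of treatment is legitimate, if less efficient. All of this stands, and it rules out several stronger readings that a reader might infer:

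- *The week-12 comparison is biased.* It is not. The ambiguity of a score of 3 concerns one patient, not the contrast between randomised arms.
- *The score mostly reflects who was better or worse off at entry.* The assumed correlations put 9% to 36% of the variance down to baseline, which leaves 64% to 91% unexplained by it.
- *A baseline imbalance would be invisible.* The patient-completed MNSI history and the DSQL are taken at baseline, as is nerve conduction. They are proxies and not the same item, but a marked difference in severity between the arms would show in them.
- *The missing month-6 reading is a defect.* MNSI and DSQL already cover persistence at month 6, and the primary outcome itself is not repeated then. A month-6 repeat is a preference.

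Two further objections limit the gain. The Statistical analysis section adjusts only for baseline characteristics that differ significantly between the groups, so adding the question without also planning the adjustment would not deliver the precision shown. And recruitment began in October 2016, so some patients cannot supply a baseline. Neither removes the point for patients still to be enrolled.

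**Conclusion.** The point holds as a minor one. The global assessment is a current-status item with a single stated reading, and it is the only efficacy outcome without a stated baseline. The between-arm comparison at week 12 is sound. What is lost is change within patients, a direct view of imbalance on the item, and precision: 9% to 36% of the variance, or the difference between 47 and about 52 to 73 patients per arm.

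That size rests on the assumed correlation of 0.3 to 0.6, on treating the grades as a numerical score, and on every analysed patient having a baseline. It bears on a supporting outcome that the abstract does not list, and it leaves the trial's sample size and primary analysis untouched. The schedule of assessments (Fig. 3) could not be seen. If it lists a baseline for this item, the fault is instead a discrepancy between the figure and the text.

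**What to change.** Ask the same single question at the baseline visit, before randomisation, and state in advance that the arms will be compared at week 12 adjusted for the baseline score, whether or not the arms differ significantly on it. If Fig. 3 already shows a baseline, correct the section text to match.

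Keep patients already enrolled without a baseline value in the between-arm comparison of week-12 status, and report that comparison for all randomised patients. Because these patients cannot supply the value, the gain in precision for the whole trial will be smaller than the range above. State for this item how missing week-12 answers will be handled where there is no earlier value to carry forward.

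The cost is one question at a visit where patients already complete the MNSI history and the DSQL, plus a protocol amendment; no new visit or staff are needed. Repeating the item at month 6 is optional.
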